### Interventions

Figure 1 is a flow diagram showing study inclusion.

**Fig. 1 Fig1:**
[figure not shown]
Flow diagram of virtual reality exposure therapy for patients with psychosis (VRETp). A figure showing the flow of patients in the study protocol

### Treatment as usual (TAU)

Participants in both the VRETp and the waiting list condition receive TAU, consisting of antipsychotic medication, and treatment and/or supportive counseling by therapists, caseworkers or coaches. TAU is considered to be equal in both conditions as a result of the randomization procedure used (see “Randomization”). During the trial participants are not allowed to receive any therapy aimed at improving social participation.

### Virtual reality exposure therapy (VRET)

VRETp treatment has a maximum of 16 treatment sessions of 60 minutes each. This number of sessions is somewhat larger than is usual for CBT in anxiety disorders. Our rationale for this is our expectation that treating paranoia requires more time compared with treating regular anxiety. People suffering from a psychotic disorder often show severity and durance in their social avoidance. Negative symptoms make it difficult to motivate people for therapy and this is a continuing process during treatment. The treatment protocol states that the therapists receive 16 hours of training; all therapy sessions are recorded. A selection of the sessions is rated for treatment fidelity using the Cognitive Therapy Rating Scale (CTRS). The CTRS is a reliable [41] and valid [42] instrument to measure treatment fidelity when following a CBT protocol. Monthly 4-hour group supervision serves to guide the therapists throughout the intervention period.

Existing CBT protocols will be adapted for VRET treatment in one area: exposure in vivo will be replaced by VR exposure. The remainder of the treatment protocol consists of well-known, evidence-based CBT elements, e.g., providing treatment rationale, behavioral experiments, reducing safety behavior, and attention training. Starting with exposure exercises for social situations, which are lowest in the patient’s anxiety hierarchy, the exposure exercises take place during the therapy session using the Virtual Reality system. Participants are not allowed to receive any other form of therapy aimed at improving social participation during the trial. At all times the therapist is in control of the VRETp intervention and is able to immediately change/stop the virtual environment if necessary.

### Early completions

A participant is considered an early completer of treatment when the subjective units of distress on a scale of 0 (no stress at all) to 100 (extremely stressful) in all the virtual situations that are part of the case conceptualization are reduced to zero in two consecutive sessions. This criterion is restrictive and was chosen to prevent therapies being ended prematurely, since no point of reference has been established for treating paranoia using VR exposure.

### Discontinuation

Participation is completely voluntary and participants can withdraw from participation at any time for any reason. Participants who drop out or otherwise deviate from the intervention protocol are requested to continue to participate in the measurements.

### Fidelity checks

Audiotapes are made of all sessions and a selection of them is rated for treatment fidelity. All therapists are supervised by a highly skilled professional ([name]) to evaluate, guide and approve the case conceptualization. Every 6 weeks, 4-hour group supervision supports the therapist for the duration of the intervention. By means of a questionnaire, for each session the therapist reports on the elements and steps in the treatment protocol. Any deviation from the protocol is reported to the supervisor.

### Unblinding

The study is single-blinded, meaning that research assistants who do the measurements are kept blinded regarding randomization of the participants. Participants are regularly instructed not to tell the research assistants which group they are allocated to; if a research assistant is accidentally unblinded during a measurement, that measurement is stopped. A new appointment is then made with another blinded research assistant.

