## Background

A large number of patients with a psychotic disorder participate poorly in society, even if their psychotic symptoms have been treated successfully. Unemployment is high at 80–85 % [1] and about 75 % do not have a relationship with a partner [2]. A study comparing the social network of young people with early psychosis and matched controls showed that the psychosis group had smaller networks, fewer friends, fewer people to turn to in a crisis, and a greater likelihood of service providers as members [3]. Social network size is also associated with the likelihood of in-patient treatment and with the number of services used by psychotic patients [4]. Social isolation hinders patients in multiple areas of functioning, such as developing and maintaining a social network, the ability to function in work-related environments, and even in performing daily tasks needed for independent living (e.g., shopping for groceries). When psychotic disorders are in partial remission, the remaining feelings of paranoia and delusions of reference often cause patients to avoid places and people. Moreover, this conditioned avoidance does not improve with antipsychotic medication [5].

**Table 1 Tab1:** Measurement objectives

Outcome	Measurement	T0	T1	T2	T3	T6
	Interview (i) Self-report (s)	Baseline	Session 4	Session 8	Posttreatment	Follow-up
Social participation	Experience Sampling Method (s)	x			x	x
Paranoia	GPTS (s)	x	x	x	x	x
Interaction anxiety	SIAS (s)	x	x	x	x	x
Depression	BDI-II (s)	x			x	x
Stigma	ISMI (s)	x			x	x
Schemas	BCSS (s)	x			x	x
Safety behavior	SBQ (i)	x			x	x
Cognitive biases	DACOBS (s)	x			x	x
Social functioning	SOFAS (i)	x			x	x
Quality of life	MANSA (i)	x			x	x
Cost-effectiveness	TIC-P (i)	x			x	x
Cyber sickness	SSQ (s)		x	x		
Presence	IPQ (s)		x	x		
Medication adherence	BARS (i)	x	x	x	x	x

*GPTS* Green et al. Paranoid Thought Scales, *SIAS* Social Interaction Anxiety Scale, *BDI-II* Beck Depression Inventory, *ISMI* Internalized Stigma of Mental Illness, *BCSS* Brief Core Schema Scales, *SBQ* Safety Behavior Questionnaire – persecutory delusions, *DACOBS* Davos Assessment of Cognitive Biases Scale, *SOFAS* Social and Occupational Functioning Assessment Scale, *MANSA* Manchester Short Assessment of quality of life, *TiC-P* Trimbos/iMTA questionnaire for Costs associated with Psychiatric illness, *SSQ* Simulator Sickness Questionnaire, *IPQ* Igroup Presence Questionnaire, *BARS* Brief Adherence Rating Scale

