### Cost-effectiveness

The Trimbos/iMTA questionnaire for Costs associated with Psychiatric illness (the TiC-P) is designed for self-report by patients with a mental disorder. The questionnaire focuses on establishing direct medical costs and productivity costs during paid or unpaid work. The psychometric properties are reported to be adequate [40].

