### Procedure

Patients with a chart diagnosis of schizophrenia, schizophreniform disorder, schizoaffective disorder, delusional disorder or psychotic disorder not otherwise specified (NOS), will be informed about the study by their treating specialist and asked to participate. Each patient is asked for written permission to be contacted by the researchers if eligible for VRETp. If eligible, the treating specialist discusses participation of the patient in the study with the remainder of the team and gives permission to the researchers to contact the patient. When permission is given, additional information is provided and patients have 2 weeks to consider whether they really wish to participate. The VRETp treatment is additional to current treatment and declining to participate has no negative consequences at all for patients. For each of the participating organizations an independent specialist is available for patients to contact. Contact information of this specialist is available in the information letter given to the patients of the participating organizations.

Informed consent from all participants is obtained before assessment by the researcher. The MINI-Plus interview is used to diagnose psychotic disorders. Patients who are willing to participate are screened for avoidance behavior (SBQ) and for paranoia using the GPTS (cutoff >40) of Green et al. Baseline measurements are obtained. Randomization is used to allocate a patient to either the VRETP or to the waiting list condition. Patients allocated to the VRETp group start their treatment, which consists of a maximum of 16 sessions with a maximum duration of 60 minutes each.

At baseline (T0) the research assistant assesses the baseline measurement of all primary and secondary variables. At 2 weeks (T1) and 4 weeks (T2) into treatment, respectively, participants in the treatment condition are assessed for their scores on paranoia, interaction anxiety, cyber sickness, presence in the virtual world and medication adherence, using self-report questionnaires handed out by the therapist, or interview questions (medication adherence).

At the end of treatment (T3) and at follow-up (T6), the research assistant assesses the primary and secondary measures.

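### Table 1 has the TiC-P cost questionnaire taken by interview, which risks revealing allocation to the blinded research assistant, mainly at T3

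*Protocol article*

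**What the plan says.** Table 1 of the protocol article gives every instrument a mode code, i for interview or s for self-report. The TiC-P carries the code i and is scheduled at T0, T3 and T6.

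The Cost-effectiveness section says of the same instrument that it "is designed for self-report by patients with a mental disorder". On content it says: "The questionnaire focuses on establishing direct medical costs and productivity costs during paid or unpaid work". It gives neither the items nor the recall period.

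The Procedure section sets out who assesses after treatment: "At the end of treatment (T3) and at follow-up (T6), the research assistant assesses the primary and secondary measures". No other assessor is named for those two visits.

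The Unblinding section says that "research assistants who do the measurements are kept blinded regarding randomization of the participants". It adds: "Participants are regularly instructed not to tell the research assistants which group they are allocated to". If blinding fails, "if a research assistant is accidentally unblinded during a measurement, that measurement is stopped", and then: "A new appointment is then made with another blinded research assistant". The cost interview is not exempted.

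**The concern.** Assessor blinding is the only blinding in this trial, because patients and therapists are told the allocation. A resource-use interview is an unsuitable task for a blinded rater here, since the main planned difference in care between the arms is the allocated treatment itself. A VRETp patient who answers fully about recent medical care may mention the sessions. One who is guarded, having been told not to reveal the group, may answer incompletely.

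At stake is the independence of the ratings that the same assistant makes at that visit. The SOFAS matters most, because it is a named secondary outcome and rests on the rater's own judgement.

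**Working it through.** **Inputs**

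- Mode of the TiC-P: interview (Table 1); self-report by design (Cost-effectiveness section).
- Assessor at T3 and T6: the research assistant (Procedure), blinded (Unblinding).
- Extra contacts in the VRETp arm: at most 16 sessions of 60 minutes (section on VRET). The waiting list is offered VRETp only after the 6-month follow-up (Design).
- Pace: Table 1 labels T1 and T2 as sessions 4 and 8; the Procedure section dates them at 2 and 4 weeks.
- Sample size: 64 per arm, 80 after 20 % attrition (Power and sample size calculation).
- A separate record of sessions: a therapist questionnaire for each one (Fidelity checks).

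**Step 1: the sections side by side.** Table 1 makes the TiC-P an interview. The Procedure section gives the T3 and T6 assessments to the research assistant. The Unblinding section keeps that assistant blind. Together they have a blinded person asking patients about medical care use. T0 is not affected, because baseline is completed before randomization.

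**Step 2: the safeguard.** The stop-and-rebook rule treats unblinding as an accident. Here the source is part of the visit. The second assistant brings the same questionnaire and meets the same risk.

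**Step 3: number of patients.** The plan's own figure reproduces. A two-sided t test with effect size 0.5, alpha 0.05 and power 0.8 needs 63.77 per arm, rounded up to 64, and 64 / (1 − 0.20) = 80. The VRETp patients interviewed at T3 therefore number between 80 × 0.80 = 64 (all attrition before T3) and 80 (none).

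**Step 4: difference in contacts.** Up to 16 × 60 min = 960 min, or 16 hours, per VRETp patient.

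**Step 5: T3 against T6.** Four sessions in 2 weeks is two a week, so 16 sessions take 16 / 2 = 8 weeks at that pace. As an assumption, take T3 and T6 as 3 and 6 months from baseline, about 13 and 26 weeks. The last session then falls 13 − 8 = 5 weeks before T3 and 26 − 8 = 18 weeks before T6. If treatment instead runs right up to T3, the gaps are 0 and 13 weeks. A recall period beyond 0 to 5 weeks reaches the sessions at T3. At T6 it must exceed 13 to 18 weeks. If the T6 questionnaire covers only the time since T3, it meets no VRETp sessions.

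**Step 6: outcomes reached.** Five of the 14 rows in Table 1 are coded as interview: SBQ, SOFAS, MANSA, TiC-P and BARS. The other nine, including the ESM primary outcome, the GPTS, the SIAS and the BDI-II, are self-report. Among the interview measures the SOFAS depends most on the rater. The SBQ frequency is given by the patient, and the MANSA records the patient's own satisfaction.

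**The case against.** The best case for the plan has five parts.

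- **The instrument may be completed on paper.** The Cost-effectiveness section points that way, and then the mechanism largely disappears. This stands, but Table 1 is then wrong and needs correcting.
- **The questions may not reveal the arm.** No items are listed, and both arms receive usual care that can include contacts with therapists, caseworkers or coaches. A plain count of contacts need not identify the group. This stands as a limit: disclosure is a risk inferred from the stated content and not a certainty.
- **The Procedure sentence does not name the TiC-P.** True, but cost-effectiveness is a listed secondary objective and no other assessor is given for T3 or T6.
- **Instrument order and staffing may be in the full protocol.** They may, and their absence from an article is no fault. The point rests on the mode that Table 1 does state.
- **Harm to the ratings requires the TiC-P to come before them at the visit.** This stands. No order is stated, and placing it last would protect that visit's ratings.

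A reader might go further and infer a forced choice: either blinding breaks, or VRETp costs are under-counted and cost-effectiveness is flattered. The documents do not support that. Nothing says that sessions are costed from the TiC-P, and the therapists' reports give a separate count. Patients are asked to conceal their group, not to leave out care contacts.

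A reader might also count 80 × 2 = 160 exposed interviews. That ignores the plan's 20 % attrition and assumes a T6 recall period long enough to reach treatment, which is not stated.

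**Conclusion.** The point holds as a risk to assessor blinding created by how Table 1 codes one instrument, together with a conflict over mode between Table 1 and the Cost-effectiveness section. About 64 to 80 VRETp interviews at T3 are exposed, and T6 adds to this only with a long recall period. The rebooking rule does not remove the risk.

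The conclusion assumes that Table 1 is followed as written, that the research assistant takes the TiC-P, and that questions on direct medical costs can bring up therapy sessions. The size of any bias in the SOFAS cannot be computed from the documents. The primary outcome is not rated by the assistant and is not threatened by this route, and the sample size is unaffected. The change is worth making because it protects the trial's only blinding at little cost.

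**What to change.** Change the TiC-P code in Table 1 from i to s, which also brings it into line with the Cost-effectiveness section. Have the patient complete it after all interview ratings at the visit, and return it so that the blinded assistant does not see it. State that the number of VRETp sessions used for costing comes from the therapists' per-session reports described under Fidelity checks.

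This takes one table entry, a sentence on visit order and a sentence on the source of session counts. It needs no extra staff or visits. The likely downside is small: possibly some more missing items than an interview would leave, an amount that the documents do not allow one to estimate.

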### Adverse events

The rules and regulations of the Medical Ethics Committee concerning adverse events are followed. All participants are insured in case any harm is caused related to trial participation.

### Analyses

#### Data management

All data are directly coded with a number. Data and personal information of the participants are kept separately and safely stored to ensure privacy. All data entry is double-checked. A data monitor from Parnassia Psychiatric Institute is appointed for the study.

#### Data analysis

Multilevel linear mixed modeling is used to analyze the data according to the intention-to-treat principle. Completer analysis is conducted with analysis of variance (ANCOVA). Moderator and mediator analysis is conducted to assess the effects of moderators and mediators. Cost-effectiveness is conducted with social participation as the outcome.

### Ethics

Ethical approval of the protocol was granted by De Medisch Ethische Toetsingscommissie VU medisch centrum (METC number: NL37356.058.12).

## Discussion

The main goal of the study is to investigate the effect of VRETp on improving social participation in patients with psychosis in real life. We hypothesize that VRETp will increase social participation objectively (time spent in company) and subjectively (experience less anxiety and paranoia during in social situations). Comparison between VRETp treatment and a waiting list condition will provide information about the effectiveness of VR exposure therapy for this population. This should make an important contribution to treatment options for people suffering from psychosis and social isolation. Improving social participation is of great personal value to patients with psychosis who suffer from the consequences of avoiding social situations in daily life.

In addition to social participation, the effect of VRETp on psychological, emotional and social well-being, especially paranoia and interaction anxiety, is explored. Studying these variables may help disentangle the complex phenomena related to social participation in patients with psychosis.

Another aspect of the study is cost-effectiveness. If social participation improves it is expected that patients will become more independent, consume less care and, thereby, diminish costs related to extended health care.

### Trial status

Ongoing.

## Abbreviations

BARS: Brief Adherence Rating Scale
BCSS: Brief Core Schema Scales
BDI-II: Beck Depression Inventory
CBT: Cognitive behavioral therapy
CTRS: Cognitive Therapy Rating Scale
DACOBS: Davos Assessment of Cognitive Biases Scale
ESM: Experience Sampling Measurement
GPTS: Green et al. Paranoid Thought Scales
IC: Informed consent
IPQ: Igroup Presence Questionnaire
ISMI: Internalized Stigma of Mental Illness
MANSA: Manchester Short Assessment of quality of life
MINI: Mini International Neuropsychiatric Interview
RCT: Randomized controlled trial
SBQ: Safety Behavior Questionnaire – persecutory delusions
SIAS: Social Interaction Anxiety Scale
SOFAS: Social and Occupational Functioning Assessment Scale
SSQ: Simulator Sickness Questionnaire
TAU: Treatment as usual
TiC-P: Trimbos/iMTA questionnaire for Costs associated with Psychiatric illness
WAIS: Wechsler Adult Intelligence Scale
WISC: Wechsler Intelligence Scale for Children
VR: Virtual reality
VRET: Virtual reality exposure therapy
VRETp: Virtual reality exposure therapy for patients with psychosis
